## Statistics and data analysis

### Sample size

We will measure social contact rates every 2 weeks in a panel of 500 individuals using diary-based methods. The precision around the average number of daily contacts in any age group will depend on the actual average number of daily contacts and degree of overdispersion in the distribution of the number of contacts. We estimate that with two records per individual we can detect a difference of 2.5 contacts between pairs of observations with 90% power, 5% Type 1 error, and 20% loss to follow up. Therefore repeated measurement of individuals should provide adequate power for further assessment of other endpoints.

### Statistical analysis

We will use multilevel count models such as negative binomial regression techniques to assess the age-specific number of daily contacts, and control for confounding factors such as sex and household size. We will perform a stratified analysis by contact type (all contacts, only physical contacts, only nonphysical contacts) and setting (e.g. household, workplace, school, social settings).

The effect of any social distancing control on the average number of contacts per day will be estimated accounting for age in the multi-level model. Further to this, the individual social distancing measures will be evaluated separately. Effect modification by age and sex will be explored as appropriate.

In order to develop social contact matrices that can be used to parametrize epidemiological transmission models. We will estimate age-specific transmission parameters by correcting the age-specific daily frequency of social contacts between different age groups for the reciprocity of contacts, adjusting for the population age distribution. These estimates will be used in ongoing and future response work conducted by LSHTM and partners to help inform public policy.

We will conduct descriptive analyses of household and individual level exposures to social distancing interventions, and uptake of individual preventive measures. Frequencies will be presented in tables and exploratory analysis of the association of these measures on the number of contacts will be performed in the multilevel count models with a random effect for

participants. Attitudes and risk perceptions relating to the Covid-19 epidemic will be assessed over time visually and using descriptive statistics.

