# Measuring Behavioural Change during Covid-19 Epidemic

## Introduction and Rationale

Appropriate response to Covid-19 requires an understanding of the epidemiological and behavioural drivers of disease transmission. Due to the dynamic nature of the epidemic and with the spread of the disease in the UK and Europe, analyses of the main factors affecting transmission need constant updating to provide relevant data-driven evidence to inform public health policies.

The predictive capabilities of mathematical models have been transformed through quantifying social contact rates. However, these data (such as the POLYMOD survey) were collected in “peace-time” and individuals’ behaviour may change during a severe epidemic.

Social mixing, a key determinant of COVID-19 spread, is likely to change over the course of the epidemic in relation to health risk perception. Therefore, timely data on social contacts and uptake of protective behaviours will be needed for shaping public health messaging and monitoring its effectiveness. These data will also be essential for improving transmission models and forecasting.

We will conduct a contact survey to assess changes in social mixing in relation with health risk perception. We will monitor contact patterns in the United Kingdom, Belgium and the Netherlands populations over the course of the epidemic, and assess psychological factors associated with contact. Behaviour tracking will be integrated in real-time models to improve the efficacy of public health interventions (e.g. messaging) and epidemic forecasts. These data will be used to refine transmission models, improve forecasting, and assess the effectiveness of social distancing measures.

We will simultaneously ask participants about knowledge, uptake and perceived efficacy of certain interventions (such as home-working). We will ask about cases in their social networks and the country, and measure how their behaviours change if/when they become unwell. Linking (at an individual-basis) changes in perceived and actual risk and changes in perceived efficacy of interventions with the uptake of different precautionary behaviours and individuals actual contact patterns will give unparalleled quantitative insight into how and why behaviours change during an epidemic.

Individuals will be regularly surveyed (every 2 weeks) to track if behaviours alter and what influences this. To our knowledge, this is the first time such data will be collected over the

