## Aim and objectives

This study aims to identify the impact of social distancing interventions implemented by the government and the perceived and actual threat of the Covid-19 epidemic on social mixing behaviours.

We will do so using the following objectives.

1. To collect accurate estimates of the following data during the Covid-19 outbreak
  - a. Frequency of age-specific social contacts and their characteristics, at different points in the epidemic
  - b. Household and individual level exposures to social distancing interventions
  - c. Uptake of individual preventive measures
  - d. Changes in attitudes and risk perceptions regarding the Covid-19 epidemic
2. To create social contact matrices that can be used to parametrize epidemiological transmission models
3. To assess the impact of different social distancing interventions on social mixing within the population
4. To use mathematical models to inform public health policy decisions related to Covid-19 outbreak.

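### The aim and Introduction promise to relate perceived and actual threat to social mixing, but risk perception is assigned only to plots and description and no listed analysis relates it to contacts or precautions

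*Protocol*

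**What the plan says.** Protocol, Aim and objectives: one aim with two kinds of exposure and one outcome. The exposures are government distancing interventions and "the perceived and actual threat of the Covid-19 epidemic on social mixing behaviours".

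Protocol, Introduction and Rationale, says this in three further ways:
- the purpose of the survey: "We will conduct a contact survey to assess changes in social mixing in relation with health risk perception";
- the intention to "assess psychological factors associated with contact";
- the individual-level promise: "Linking (at an individual-basis) changes in perceived and actual risk and changes in perceived efficacy of interventions with the uptake of different precautionary behaviours" and with each person's contact patterns.

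The numbered objectives are narrower. Objective 1d is a data-collection item: "Changes in attitudes and risk perceptions regarding the Covid-19 epidemic". Objective 3, the only one about impact on mixing, reads "To assess the impact of different social distancing interventions on social mixing within the population" and does not mention threat.

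Protocol, Statistical analysis: contacts are modelled by multilevel count regression with age, confounders and distancing measures. An exploratory association with contacts, using a participant random effect, follows for intervention exposures and preventive measures. Risk perception then has a sentence of its own: "Attitudes and risk perceptions relating to the Covid-19 epidemic will be assessed over time visually and using descriptive statistics".

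**The concern.** A description over time shows how risk perception moved from survey to survey. It does not show whether people whose perceived risk rose cut their contacts or took up more precautions, which is what the aim and the Introduction say the study will find out. The protocol does not merely leave the method open for risk perception: it states one, and that method cannot estimate the promised link.

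The Dissemination section plans release within days of each survey wave to support decisions on interventions, and the Introduction names public messaging as a use. If risk perception and contacts are shown only as trends, readers may draw the individual-level conclusion themselves, with no estimate or interval behind it.

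**Working it through.** The point is one of consistency, so the check sets each promised exposure against the analyses listed under Statistical analysis.

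| Exposure in the aim or Introduction | Collected? (Survey section) | Listed analysis against number of contacts |
|---|---|---|
| Distancing interventions | Yes, every survey | Main model, individual measures separately, and exploratory association |
| Preventive measures | Yes | Exploratory association |
| Perceived threat (risk perception) | Yes, over time; frequency not stated | None; visual and descriptive |
| Actual threat (symptoms, tests, known-case contact) | Yes, every survey | None named |
| Perceived efficacy of interventions | Promised in the Introduction, not itemised in the Survey section | None named |

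**Could the exploratory sentence include risk perception?** The measures it refers to are those just named: exposures to interventions and uptake of preventive measures. Risk perception comes afterwards, with a different method, so the grammar does not carry it into the model.

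**Is uptake of precautions modelled as an outcome?** No. It is tabulated and used as an explanatory variable for contacts. The promised link from risk perception to precautions therefore has no analysis either.

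**Data available (Enrolment procedure: 500 adults per country, five surveys):**
- records per country: 500 x 5 = 2,500, an upper bound;
- three countries: 3 x 2,500 = 7,500, an upper bound;
- records that have a previous survey's score: 500 x (5 - 1) = 2,000 per country, again at most.

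The Sample size section assumes 20% loss to follow-up. Leavers are replaced by new panel members, who contribute fewer surveys. Within-person information comes only from people with two or more surveys, so usable numbers will be lower.

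**Does the sample size statement cover this question?** It concerns a difference of 2.5 contacts between paired observations, with 90% power and 5% type 1 error. It cannot be reproduced because no standard deviation is given. Solving backwards with 500 x 0.80 = 400 pairs and a two-sided test:

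SD of paired differences = 2.5 x sqrt(400) / (1.960 + 1.282) = 50 / 3.242 = about 15.4 contacts.

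The statement is consistent if the SD is near that value. It concerns change in contacts, not an association with risk perception, and the present point does not depend on it.

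**The case against.** The best defence is that the protocol pursues its aim through the numbered objectives, and the analysis section matches them: models for interventions, contact matrices, and description for objective 1d. On that view the aim and Introduction are loosely worded and nothing is missing. This stands in part. It places the break between the aim and Introduction on one side and the objectives and analysis on the other, and makes narrowing the aim a legitimate repair. It does not remove the contradiction.

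A second defence is that the confounder list is open-ended, that the risk-perception sentence does not say description is the sole use, and that a statistical analysis plan, not at hand, may add models. For perceived threat this is weak: an exposure named in the aim is not a confounder, and the protocol gives it a stated method. For actual threat it has force. The sentence on risk perception says nothing about symptoms, tests or known-case contact, and that half rests only on their absence from the section.

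Four stronger readings are tempting but not supported:
- **That within-person linkage goes unused.** The participant random effect links repeated records for interventions and preventive measures; only the link to risk perception is unspecified.
- **That the analysis shrinks to five points per country with a correlation near plus or minus one.** The protocol does not say that description means one mean per survey, and no such correlation has been shown.
- **That every item needed is already asked at every survey.** The Survey section does not say so for risk perception, and does not itemise perceived efficacy or national case numbers.
- **That the other results are compromised.** Nothing shows this.

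**Conclusion.** The concern holds for perceived threat: the aim and Introduction promise an individual-level relation with mixing and precautions, and the stated method for risk perception cannot provide it. For actual threat it holds as an inference from silence. The size is qualitative: no estimate and no interval are planned for that part of the aim, against an upper bound of 2,500 records per country that could inform one.

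Severity is moderate. Contact estimates, contact matrices and intervention effects do not depend on the missing analysis, and adding it needs no new recruitment. The conclusion assumes that the Statistical analysis section lists the intended analyses; the feasibility of the first remedy below also assumes that risk perception is asked repeatedly of the same people.

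**What to change.** Choose one of two repairs.

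**1. Add the analysis.** In the Statistical analysis section:
- Enter the risk-perception items as a time-varying exposure in the planned multilevel negative binomial contact model with a participant random effect. Split them into the person's mean and the deviation from it, so that within-person and between-person effects are separate. Adjust for survey wave, country and interventions in force.
- Include own symptoms and contact with known cases as actual-threat exposures.
- Fit a matching multilevel logistic model for uptake of precautions.
- Use perceived efficacy only if it is collected at each survey. Leave out national case count where wave effects are in a single-country model, since it has one value per wave and is then fully collinear with them.
- Report associations, not effects, because risk perception and contacts are measured in the same survey. As a sensitivity analysis use the previous survey's score, with at most 2,000 records per country before loss and replacement.
- Keep the plots as description, and state that risk perception is asked at every survey.

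**2. Narrow the claim.** Reword the aim and the Introduction so that risk perception is described over time, and drop the promise of individual-level linking.

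The first costs extra analysis work only, provided the items are asked as assumed. The second costs only a change of text, but gives up that part of the question.

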## Regulatory details

We apply for ethics approval at LSHTM Research Ethics Committee. Further ethics approval will be sought where required.

Informed consent will be obtained prior to any respondent completing the first survey. All panel members will already have given their consent to be included in the internet panel and to be approached for online research. We will inform participants about the rationale and topic of the survey, and the incentive they will receive upon completion. They will need to provide their explicit consent before the survey will start.

The right of the participant to refuse to participate without giving reasons will be respected at all times. All participants are free to withdraw at any time from the survey without giving reasons.

The survey will be translated to Dutch, Flemish, and French, and back translated to English to ensure the meaning of each question will remain as intended.

All data will be stored securely and confidentiality will be protected in accordance with the Data Protection Act.

## Dissemination of findings

Findings will rapidly be made available on online sources within several days of completion of every wave of the survey. This will allow for rapid dissemination to improve public health policy decision making, specifically regarding putting interventions in place, and up-, or downscaling interventions. The anonymised data will be made publicly available.
